##### Blood sampling

20 mL of peripheral blood will be sampled from each patient at times 0, 6, 12 and 18 months. During the OGTT at times 0, 12 and 18 months, an additional amount of 10 mL will be drawn 120 min after the glucose load. Collected blood samples will be stored at − 80 °C until shipment to UNIBO and HSJD for analysis (see below).

#### Assessment of outcomes

##### Ovulatory function

Salivary progesterone will be centrally analysed at HSJD using an Enzyme-Linked Immunosorbent Assay (ELISA) [IBL-TECAN, Hamburg, Germany; intra- and inter-assay coefficients of variation (CVs) of 4.9 and 6.7%, respectively; salivary progesterone in the luteal phase, range: 87–550 pg/mL].

Saliva samples are a non-invasive, feasible method for monitoring progesterone levels across the menstrual cycle as they can be self-collected at home and stored in a home freezer for months before analysis [93]. Salivary progesterone concentrations are closely related to unbound serum progesterone [94]. This method has been previously used to assess ovulation rate in adolescents with type 1 diabetes and polycystic ovarian morphology [95, 96]; in one pilot study performed in HSJD, serum progesterone assessed by immuno-chemiluminescence, and salivary progesterone measured by the proposed method were highly correlated (*r* = 0.84; *p* < 0.0001; unpublished results). Two pilot studies performed in adolescent girls with PCOS have confirmed the reliability of salivary progesterone measurements [14, 15].

Information from salivary progesterone measurements and from menstrual diaries will be combined to infer ovulations and annualised ovulation rates. In the two previous pilot studies performed at HSJD [14, 15], with a similar ELISA method no longer available (Novatec, Immundiagnostica, Dietzenbach, Germany; intra- and inter-assay CVs < 10%), candidate ovulations were identified using a lower salivary progesterone cut-off of 99 pg/mL, as recommended by the manufacturer. All the ovulations that were confirmed by the above-mentioned two-step process were associated with salivary progesterone concentrations > 150 pg/mL. The progesterone cut-off derived from the ELISA assay to be used in the present study will be updated/rewritten when the new assay/method has been tested/validated. Candidate ovulations will be confirmed if the menstrual calendar mentions that menses did occur at least 2 weeks before and at most 2 weeks after obtaining the concerned saliva sample.

##### Clinical variables

In each centre, the same investigator willmeasure height and weight to infer BMImeasure waist and hip circumference to infer WHRmeasure SBP and DBP with an electronic sphygmomanometer on the right arm after a 5-min rest, with the participant supineassess hirsutism by modified Ferriman-Gallwey score [22, 82] and acne by Leeds grading scale [84]take a history including information about menstrual regularity and the intake of concomitant medication

##### Endocrine-metabolic markers

*Androgens:* for enrolment purposes, circulating testosterone, SHBG, androstenedione and dehydroepiandrosterone-sulphate will be measured in referring/participating centres, and FAI will be derived. At times 0, 6, 12 and 18 months in the actual study, SHBG will be measured in the patient’s centre (by immuno-chemiluminiscence) whereas the steroid profiling (including testosterone and androstenedione) will be performed by liquid chromatography-tandem mass spectrometry (LC–MS/MS) at UNIBO [85, 97].
*Lipids:* total cholesterol, LDL-cholesterol, HDL-cholesterol and triglycerides will be assessed in the patient’s centre by molecular absorption spectrometry.
*Fasting insulin and glycaemia, and glucose-stimulated insulinaemia (OGTT):* insulin resistance will be estimated from fasting insulin and glucose levels with the homeostasis model assessment (HOMA-IR; CIGMA calculator programme v2.00) [14, 15, 98]. Standard OGTTs (75 g of glucose) will be performed after an overnight fast, as recommended [99]. Blood will be sampled before and 2 h after glucose intake for both glucose and insulin measurements, and their *Z*-scores will be derived [14, 15, 27]. Glucose will be measured by the glucose oxidase method and insulin by immuno-chemiluminiscence.
*Markers of inflammation and insulin sensitivity:*
Serum us-CRP levels will be measured by immuno-chemiluminescence at participating centres.Circulating CXCL14 will be measured by a specific ELISA kit (RayBiotech, Nocross, GA, USA) with a sensitivity of 0.7 ng/mL, and with intra- and inter-assay CV < 12% (74).Circulating HMW-adip will be measured by ELISA (R&D Systems, Minneapolis, MN, USA) with intra- and inter-assay CVs < 9%, as reported [14, 15].Circulating GDF15 will be measured by a specific human ELISA kit (R&D Systems, Minneapolis, MN, USA) with intra- and inter-assay CVs < 6%, as reported [100].

Measurements of HMW-adip, CXCL14 and GDF15 will be centralised at HSJD.

##### Epigenetic variables

Expression levels of circulating miR-451a will be measured by a RT-qPCR-based approach [101], centralised at HSJD.

##### Imaging variables

*Cardiovascular risk:* cIMT is a non-invasive marker of cardiovascular risk. At each centre, ultrasound scans of the carotid arteries will be obtained by the same investigator (blinded to treatment allocation) and with comparable high-resolution equipment and transducers; images will be read by the same investigator (blinded to treatment allocation), stored at a central repository, and centrally validated at HSJD. The values obtained on each side will be averaged (the intra-observer CVs are expected to be < 10%).
*Body composition:* bone mineral density (BMD), bone mineral content (BMC) and body composition [fat body mass (FBM), truncal fat mass (TFM), abdominal fat mass (AFM), lean body mass (LBM)] will be assessed by DXA with comparable equipment in the participating centres and with previous phantom calibration [14, 15] and will in each centre be analysed by the same investigator (blinded to treatment allocation). Images will be stored at a central repository and will be centrally validated at HSJD.
*Abdominal fat distribution and hepatic fat: a*bdominal fat distribution (subcutaneous and visceral fat) and hepatic fat will be analysed by MRI using comparable equipment in the participating centres. At each centre, scans will be performed by the same operator (blinded to treatment allocation), will be anonymised by the data management team (ensuring blindness to all clinical information) and will then be analysed centrally at HSJD.

A central reader (based at HSJD) will handle all imaging data and will maintain a central repository (based at QUIBIM, Valencia, Spain) wherein the images will be available for analysis.

##### Lifestyle

The effectiveness of lifestyle intervention will be evaluated by assessing changes in:Imaging parameters (by DXA, MRI and cIMT)Clinical variables (including BMI)Endocrine-metabolic variables (including lipids and usCRP)Health behaviour assessed through a questionnaire on physical activity, eating behaviour and nutrition [questions adapted from HBSC questionnaire [102]]Minimisation of adverse side effects, mainly aggravation of unfavourable eating behaviour [103] and evaluation of the risk of eating disorders assessed through the SCOFF and the first question of BEDS-7; only in case the risk is confirmed, then, the EDE-Q will be used which covers the four subscales of restraint, eating concerns, weight concern and shape concern [104].Adherence to LIP (completion of session preparation task).PROMS on HRQoL [generic (SF-36) and specific (PCOSQ) questionnaires (see below)].

##### Safety variables assessment

*Laboratory safety variables:* blood count (by flow cytometry and colorimetric assay), electrolyte panel, ALT, AST, GGT, urea, creatinine (by molecular absorption spectrometry), vitamin B12 and folic acid (by immuno-chemiluminescence) will be assessed locally at each participating hospital.
*Pregnancy test:* before treatment start, a highly sensitive serum HCG pregnancy test will be performed. During the study, pregnancy tests will be performed 3-monthly, either by highly sensitive serum test, or by a standard sensitive urine test detecting HCG concentrations > 25 mIU/mL.
*Report of AEs:* all AEs will be recorded in the medical history and subsequently in the eCRF. The investigator will also judge whether the adverse event is related or not to the study drug, and this judgement will also be noted in the medical history and eCRF.

##### Adherence and acceptability

*Adherence:* as a marker of adherence to intervention, the ratio will be calculated (and expressed in %) between the number of tablets that were ingested and those that were prescribed, the former being calculated as the difference between the number of tablets that were dispensed and those that were returned at the subsequent visit. In addition, the Intake Table of the Patient Diary will be screened to check whether the calculated ratio (or %) fits with the information registered by the patient.
*Acceptability of the tablet:* the patient’s opinion regarding the palatability and easiness to swallow the tablet (containing Placebo, PIO, SPIO or SPIOMET) will be recorded by using a simple questionnaire with numerical rating scales, adapted from reference [105] and shown at Table 6.

**Table 6 Tab6:** Tablet acceptability questionnaire

Numerical Rating Scales (NRSS) OR qualitative/descriptive controlled vocabulary for palatability/acceptability assessments of paediatric oral use formulations					
**Score**	**1**	**2**	**3**	**4**	**5**
Overall opinion of taste	Very bad	Bad	Acceptable/ OK/ Not nice and not bad	Good/ Nice	Very good/ Very nice
Overall swallowability (descriptive)	Vomits the drug immediately or within 2 h	Spat it out	Swallowed with some problems	Swallowed with no problems	
Parent/caregivers’ overall opinion on their daughter’s acceptability of the formulation	Very bad	Bad	Acceptable/ OK	Good	Very good

##### PROMs and HRQoL

The effects of PROMs on HRQoL will be assessed (at times 0, 6, 12 and 18 months) with generic (SF-36) and specific (PCOSQ) questionnaires. SF-36 consists of 36 items grouped in 8 multi-item scales. The scores on each domain range from 0 to 100; the higher scores point to a better condition using the same 8 subscales. The PCOSQ contains 26 items scoring the same 8 domains. Each item is answered by choosing from a Likert scale with 7 options, from 1 (always) to 7 (never). Questionnaire versions in languages of the participating centres/countries will be validated during the clinical trial.

### Plans to promote participant retention and complete follow-up {18b}

Participants will be seen in person during 3-monthly medical visits. Between such appointments, the study centre will stay in contact with participants (by phone) as to ensure compliance with treatment and follow-up.

If a study participant skips one study visit, thenThe clinical site (investigator or designee) will make a first attempt to contact the participant, will point to the importance of the study schedule and will make a new appointment at mutually earliest convenience, unless the participant clearly expresses the wish to abandon the study.If a first attempt to contact the participant fails, then at least three further attempts will be made by phone, by certified letter to the participant’s last known mailing address, or by equivalent routes. These contact attempts will be documented in the participant’s medical record or study file.If the participant cannot be reached by the staff of the study centre, or ends up skipping the next visit too, then she will be considered to have withdrawn from the study, due to loss of follow-up.

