#### Criteria for discontinuing or modifying allocated interventions {11b}

Study participants are free to withdraw from participation at any time upon request.

Discontinuation of the study intervention will imply discontinuation of the study and thus a dropout, so that any remaining study procedures will not be performed.

All data available until the discontinuation of the study intervention will be collected. If a clinically relevant finding is identified (including, but not limited to changes from baseline) after enrolment, the investigator or qualified designee will determine whether any change in participant management is needed. Any new clinically relevant finding will be reported as an adverse event (AE).

Criteria for discontinuing the allocated intervention are as follows: (1) pregnancy; (2) significant non-compliance with the intervention, for example, no medication intake for 30 consecutive days; in case of AE, patients are allowed to interrupt the treatment for 7 days without being withdrawn from the study; (3) any clinical AE, laboratory abnormality, or other medical condition/situation such that continued participation in the study is unlikely to be in the best interest of the participant; (4) appearance of an exclusion criterion (either newly developed or not previously recognised).

In case of premature termination of study participation, the patient will be re-allocated to the outpatient clinic as a regular patient whenever possible.

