### Concealment mechanism {16b}

Treatment allocation will be done via Interactive Web Randomisation System (IWRS) accessible through the electronic Case Report Form (eCRF) and randomisation codes will be generated. Once a patient is randomised to a planned treatment group, medication kits will be delivered according to the allocated treatment at time 0, 3, 6 and 9 months. Therefore, up to 4 medication kits will be assigned per subject. Each medication kit will contain enough medication for 3 months (3 bottles per kit; each bottle containing 35 pills).

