##### Saliva sampling

Saliva samples will be collected once weekly, on the same weekday, in the morning and in the fasting state, for 12 consecutive weeks during two timespans on-treatment (0–3 and 9–12 months) and one timespan post-treatment (12–15 months), yielding a total of 36 samples per study participant. The collection of saliva will be performed by spitting in a plastic container that will then be placed in a home freezer space (at − 20 °C), bearing a code number and also the date and time of sample collection. Samples will be kept frozen at home until transportation to the clinical centre, where samples will be processed and stored at fridge or freezing temperature. Once or twice yearly, samples will be shipped to HSJD where salivary progesterone concentrations will be measured.

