### Statistical methods for primary and secondary outcomes {20a}

The statistical objective of the study will be the assessment of the efficacy, tolerability and safety of SPIOMET in AYAs with PCOS. As explained (see the “Trial design {8}” section), the statistical analysis will be conducted with a hierarchical approach considering the mean number of ovulations (primary outcome) for the different study treatment arms following the predefined order: (1) SPIOMET vs placebo; (2) SPIO vs placebo; (3) PIO vs placebo; (4) SPIOMET vs PIO; and (5) SPIOMET vs SPIO. Therefore, the first comparison will be analysed in the first place, and only if a significant finding is detected for this comparison, a formal statistical conclusion will be reached for the subsequent comparisons (2nd, 3rd, 4th and 5th).

Each null hypothesis will be tested in all randomised patients based on the intention-to-treat (ITT) principle. The analysis will be conducted using an analysis of variance (ANOVA) considering the stratification factors used in the randomisation.

The statistical analysis will be carried out in accordance with the principles specified in the International Conference on Harmonisation (ICH) Topic E9 (CPMP/ICH/363/96) [106] and the addendum on estimands [107]. The SAS System [108] (release 9.4, or an upgraded version), or equivalent validated statistical software, will be used to analyse the data sets. Statistical tests for primary and secondary efficacy outcomes will use a significance level of 0.05; point estimates and two-side 95% confidence intervals for appropriate treatment effects will be provided.

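### The retention rule in section {18b} classes a participant as withdrawn for missed visits even if she still consents, which from month 12 onward can replace obtainable primary-endpoint data with imputed values

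*Protocol article*

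**What the plan says.** Section {18b} of the protocol article sets out steps after a skipped visit. The site contacts the participant and "will make a new appointment at mutually earliest convenience, unless the participant clearly expresses the wish to abandon the study". If the first attempt fails, at least three more follow. The rule then closes with two triggers. The first is that staff fail to reach her. The second trigger and the consequence of both read: "or ends up skipping the next visit too, then she will be considered to have withdrawn from the study, due to loss of follow-up".

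Five other places bear on this rule:

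- Saliva sampling: samples are self-collected weekly. "Samples will be kept frozen at home until transportation to the clinical centre".
- Plans for collection and assessment of outcomes {18a}: the diary, which is needed to confirm ovulations, is kept at home and delivered at the next visit.
- Concealment mechanism {16b}: "medication kits will be delivered according to the allocated treatment at time 0, 3, 6 and 9 months", with three bottles of 35 tablets per kit.
- Section {11b}: discontinuing the intervention means discontinuing the study, "so that any remaining study procedures will not be performed". Data available up to that discontinuation are collected. Thirty consecutive days without medication is the example given of significant non-compliance.
- Section {20a}: "Each null hypothesis will be tested in all randomised patients based on the intention-to-treat (ITT) principle". Under section {20c}, a patient with less than 80% of the six-month assessment has her months 0–3 data used for imputation.

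**The concern.** The two triggers in {18b} are joined by *or*. The second therefore covers a participant who answers the telephone, has not asked to leave and simply misses the next visit. She is recorded as withdrawn because of loss to follow-up, and neither description is true of her. The first trigger can act after a single missed visit if the contact attempts fail, even if she would have come to the following one.

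The primary endpoint depends little on attendance. It counts ovulations from month 9 to month 15, using saliva frozen at home and a diary kept at home; the visit is where they would ordinarily be handed in. An administrative label can thus turn an outcome that could still be observed into an imputed one. The substitute comes from months 0–3, when the section on analysis of the primary outcome expects all arms to have comparably low ovulation. The month-18 assessments (endocrine-metabolic, imaging, safety and quality of life) can end with it.

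**Working it through.** **Plan's own figure.** The only stated number that this rule feeds into is the expected number of completers: 364 × (1 − 0.27) = 265.7, or 66.4 per arm. This reproduces the stated 266 (66 or 67 per arm). The 27% is not split by reason.

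**Where does {18b} act alone?** Inputs: kits at days 0, 90, 180 and 270 (a month is 30 days in Table 4); 3 × 35 = 105 tablets per kit; treatment ends at day 360. Sections {11c} and Adherence and acceptability have unused tablets returned at the following appointment, so surplus is not carried forward. Gap = (next kit actually dispensed, or day 360) − (day of last kit + 105).

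| Visits missed (months) | Last kit lasts to day | Next kit or end of treatment | Days without tablets |
|---|---|---|---|
| 3 + 6 | 0 + 105 = 105 | 270 | 165 |
| 6 + 9 | 90 + 105 = 195 | 360 | 165 |
| 9 + 12 | 180 + 105 = 285 | 360 | 75 |
| 12 + 15 | 270 + 105 = 375 | 360 | 0 |
| 15 + 18 | 270 + 105 = 375 | 360 | 0 |

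If surplus tablets were kept instead, the second and third gaps would be 360 − 210 = 150 and 360 − 315 = 45 days. Either way, the first three pairs exceed the 30-day example in {11b}, unless a kit is supplied in between. The last two do not.

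**What can be outstanding when {18b} acts alone.** The primary window holds 12 + 12 = 24 weekly samples.

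- Months 12 and 15 missed: up to 24 of 24 may still be at home, and the month-18 visit ends.
- Month 12 missed and contact fails: 12 are at home, rising to 24 if she keeps collecting; the month-15 and month-18 visits end.
- Months 15 and 18 missed: the 12 post-treatment samples may be at home; no visit remains.

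**Link to the analysis.** If completion in {20c} is counted in samples (an assumption), 80% of 24 is 19.2, so 20 are needed. With 0 or 12 of 24 delivered (0% or 50%), the months 0–3 fallback applies.

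**Size.** No rate of such cases is given. Purely for scale, assume a fraction f of 2–5% of 364 (7 to 18 patients), equal across arms and unrelated to outcome, all filled from months 0–3 with no arm difference there. The design difference becomes 0.922 × (1 − f): 0.904 at 2% and 0.876 at 5%. For a given f this is an upper bound on the loss, because it supposes that every such patient would otherwise have supplied a complete outcome.

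**The case against.** A reader might infer that home-collected saliva is lost by rule. The documents do not say so. Section {18b} is silent on samples, Saliva sampling keeps them at home until transport without tying hand-over to a given visit, and {11b} keeps data available up to discontinuation. A condensed article may also leave retrieval to the full protocol. This objection stands: the point rests on the stated withdrawal rule, not on a claim that samples are thrown away. The {11b} sentence is only partial protection, however, because months 12–15 fall after treatment has ended.

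A reader might also infer that {18b} separately removes patients throughout the trial. It mostly does not: before month 12, {11b} would usually remove them too. For months 15 + 18 no visit is left to lose. The independent effect is therefore narrow.

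Nor should the 0.90–0.88 range be read as an estimate. Its rate is assumed, and most double absences before month 12 belong to {11b}. That skipped visits track response or side effects is plausible but not shown.

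Finally, the site must already make contact, offer a new appointment and, if the first attempt fails, try at least three more times. This limits how often the rule bites but does not change what it does. The next visit might also mean the rescheduled appointment, which would make the rule stricter, not milder.

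**Conclusion.** The concern holds in this form. Section {18b} declares a participant withdrawn through loss to follow-up after a second skipped visit, even if she is reachable and consenting, or after one skipped visit if contact fails. Her later follow-up then ends, and recovery of material held at home is not provided for. The rule acts on its own mainly from the month-12 visit onward. There, a patient who may have taken all her medication and holds 12 to 24 of the 24 primary samples can have months 9–15 filled from months 0–3. That is at odds with analysing all randomised patients by intention to treat.

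The effect on the 0.922 difference cannot be computed from the documents and is probably small. The change is still worth making, because the missing data are avoidable and the correction is cheap. The supply gaps assume 30-day months, kits dispensed only at the listed visits and return of unused tablets.

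**What to change.** Replace the last rule of {18b}:

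- Record a skipped visit as missed and keep all later visits scheduled.
- Use *withdrawn* only when the participant, or her parent or representative, withdraws consent.
- Assign *lost to follow-up* only when the month-18 window closes after failed contact attempts.
- Accept saliva and diaries stored at home whenever they are handed in, and use them in the primary analysis.

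Reconcile this with the statement in {11b} that discontinuing the intervention means discontinuing the study; otherwise the change has little effect before month 12.

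The cost is a short amendment, a few more contact attempts and longer home-freezer storage for some samples. The section on ovulatory function already regards home storage for months as acceptable.
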